## Abstract

**Background:**

There is currently a lack of randomized, sham-controlled trials that are adequately powered, using validated outcomes, to allow for firm recommendations on the use of magnetic stimulation for stress urinary incontinence. We report a protocol of a multicenter, randomized, double-blind, sham-controlled parallel-group trial to evaluate the efficacy of magnetic stimulation for stress urinary incontinence.

**Methods/Design:**

One hundred twenty subjects with stress urinary incontinence will be randomized in a 1:1 allocation to either active or sham magnetic stimulation using computer-generated, permuted blocks of variable sizes. Subjects will receive 2 sessions of magnetic stimulation per week for 8 weeks (16 sessions total). The primary outcome is the improvement in severity of involuntary urine loss based on the International Consultation on Incontinence Questionnaire for Urinary Incontinence Short Form at the end of treatment sessions compared with baseline. Secondary outcomes include cure, stress urinary incontinence–related symptoms (incontinence episode frequency, urine loss in 1-hour pad test, pelvic floor muscle strength) and health-related quality of life (Patient Global Impression of Improvement, International Consultation on Incontinence Questionnaire–Lower Urinary Tract Symptoms Quality of Life and EQ-5D). The safety of magnetic stimulation will also be assessed. Besides evaluation of clinical treatment effectiveness, cost-effectiveness analysis using patient-reported outcomes will be performed.

**Discussion:**

This trial is designed to provide pending outcome information on this non-invasive treatment option. We intend to acknowledge the existing flaws in previous clinical trials and determine conclusively whether magnetic stimulation is effective for stress urinary incontinence.

**Trial registration:**

ClinicalTrials.gov Identifier: NCT01924728. Date of Registration: 14 August 2013.

**Electronic supplementary material:**

The online version of this article (doi:10.1186/s13063-015-0803-1) contains supplementary material, which is available to authorized users.

## Background

Stress urinary incontinence (SUI) is a condition in which there is an involuntary loss of urine on effort, physical exertion, sneezing or coughing [1]. It is a chronic and debilitating condition that affects the physical, psychological, social and economic well-being of affected individuals and their families [2] and substantially reduces quality of life (QoL) similarly to severe chronic diseases such as stroke, arthritis and chronic kidney disease [3, 4]. Prevalence estimates of urinary incontinence (UI) are disparate, ranging from 7 % to 53 % [5, 6], depending on variables such as definition of UI used, survey population, methodological and cultural differences, with SUI accounting for approximately 50 % of all incontinence [2].

The current guideline advocates pelvic floor muscle training (PFMT) as the first-line conservative treatment for SUI [7]. Use of other conservative therapeutic options, such as biofeedback, vaginal cones, electrical stimulation and urethral plugs, is limited because of their side effects, discomfort and invasiveness. Although surgical interventions using midurethral slings have unquestionably superior cure rates of approximately 90 %, compared with 30 % in conventional physiotherapy [8], some patients may be medically unfit for surgery, especially elderly patients. Moreover, there is a risk of adverse events related to surgery, such as bladder perforation, vaginal epithelial perforation and hematoma [8]. Indeed, when given a choice, most patients opt for conservative treatments [9]. Treatment options should therefore be based on the collaborative efforts between patients and doctors, taking into account both the patient’s preferences and the surgeon’s judgment [10].

Given the high SUI prevalence and its overwhelming negative impact on the QoL of patients, there is a need for an acceptable therapeutic option with high efficacy. Many subsequent studies have focused on developing novel, non-invasive techniques to treat SUI, including the use of magnetic stimulation (MS). Several small studies, conducted in the United States [11, 12], Japan [13–15], Korea [16] and Turkey [17, 18], demonstrated that MS improved symptoms of SUI, with limited or no side effects. Additional file 1 provides a summary of published clinical trials on MS for SUI in more detail. We recently conducted a systematic review and found that most of the previous MS studies on SUI had flaws, including lack of a placebo group, small sample size, short or no follow-up and poor reporting [19]. The Fifth International Consultation on Incontinence emphasized that no recommendation is possible based on current evidence and that further research is needed to reduce the uncertainty around decision-making regarding the use of MS [20]. Many key issues remain. Is MS effective for female SUI? How many sessions are needed? How long can the effects last? Is maintenance therapy required? To answer these questions, a high-quality randomized controlled trial is imperative. Thus, we designed a multicenter, randomized, double-blind, sham-controlled trial with the objective of evaluating whether patients with SUI treated with MS have a higher continence rate than sham-treated patients.

### Aims of the study

The aim of the study is to investigate the effects of MS in female patients with SUI. Furthermore, we intend to show that MS therapy is safe and effective when provided in a community setting and to prove its overall cost-effectiveness. The following research questions were developed:What is the efficacy of MS in female patients with SUI?Does the use of MS lead to a better QoL in patients with SUI?Is the use of MS cost-effective compared with the conventional therapy?After the first 2 months of treatment:How effective is active MS in patients who did not respond to the initial sham treatment?Does longer treatment with active MS improve treatment response in the initial active group?

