## Methods/Design

### Study design

This is a multicenter, randomized, double-blinded, sham-controlled, parallel-group trial in a 1:1 allocation ratio. Potential subjects will be screened from among patients attending urology or obstetrics and gynecology clinics of the participating hospitals in Northern Malaysia: Island Hospital, Lam Wah Ee Hospital, Penang Adventist Hospital, Pantai Hospital, Metro Specialist Hospital and Loh Guan Lye Hospital, as well as from among the general population through advertisements in posters, brochures, newspapers and websites. The diagnosis of UI will be made by either the urologist or the gynecologist [1]. Methods, definitions and units conform to the standards jointly recommended by the International Continence Society and the International Urogynecological Association, except where specifically noted [1]. The flowchart and study design schedule are presented in Fig. 1 and Table 1, respectively.

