#### Additional restrictions

Subjects of childbearing age who are not actively conceiving are required to be on any effective contraception methods, including (1) established use of oral, injected or implanted hormonal methods of contraception; (2) placement of an intrauterine device or intrauterine system; (3) barrier methods of contraception, including condom or occlusive cap (diaphragm or cervical or vault caps) with spermicidal foam, gel, film, cream or suppository; (4) male sterilization (with the appropriate postvasectomy documentation of the absence of sperm in the ejaculate); and (5) true abstinence.

Subjects who are taking α-adrenergic antagonists or any other medications known to worsen incontinence will be recruited into the study only if the medications can be discontinued. If the medications can be discontinued, the subjects will undergo a 14-day washout period and then be reassessed for eligibility.

Subjects are prohibited from starting additional specific treatments for SUI, including PFMT, biofeedback, vaginal cone, electrical stimulation or pharmacological treatments such as duloxetine.

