**Fig. 2 Fig2:**
[figure not shown]
QRS-1010 PelviCenter magnetic stimulation device

In both groups, treatment involves two sessions of 20 minutes each per week for 8 weeks (16 sessions total). After the 8-week treatment, subjects who are not satisfied with their treatment outcome will be given the opportunity to enroll in an open-label phase, regardless of their treatment allocation. Subjects will be considered treatment defaulters if they miss treatments for more than 2 consecutive weeks.

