#### Sham magnetic stimulation

To ensure that sham subjects’ experiences are similar to the intervention, the sham group will undergo the same number, duration and frequency of treatments as the active group using the same MS device and stimulation frequency. However, unlike the intervention, the magnetic coil will be tilted to 22° down with a lower stimulation intensity, beginning with 20 % simulation intensity at the first session, followed by gradually increasing increments of 20 % intensity after every five sessions until a maximum of 60 % intensity is reached (Fig. 3). The combination of these methods has been shown to provide a total energy output of 136 kJ, (or 8.500 J each session) during the 8-week study period, which is far less than the energy output of one 20-minute active mode run (at 100 % intensity) of 408 kJ, thus providing a similar appearance as the active treatment.

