
### Health economic evaluation and analysis

In addition to the evaluation of clinical treatment effectiveness, a prospective assessment of health economic issues is being planned. A cost-effectiveness analysis using patient-reported outcomes will be performed. To estimate costs, the resource use is measured in natural units (e.g., duration of treatment in minutes). The average resource use per patient is calculated and priced with opportunity cost approximated over Malaysian market prices or schedule prices (e.g., wage agreements for staff costs). A sensitivity analysis is performed by replacing the mean costs and effects with the upper and lower bounds of the respective 95 % confidence intervals. Costs and effectiveness results are synthesized in an incremental cost-effectiveness ratio.

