MS is a non-invasive procedure and has been shown to be effective in SUI in various open-label studies [23]. Further advantages are no reported adverse events, unnecessary to undress, automatic contractions and no pain. If the efficacy of MS is better than PFMT, which has a success rate of approximately 30 %, it may be a reasonable option for patients with SUI who are not keen to undergo surgery. The results of our trial are expected to add essential confirmatory data regarding whether MS is effective for women with SUI.

Our protocol has some limitations. To maximally exclude any placebo effects, various considerations were taken when designing the sham MS. We used the same MS device, designed a coil that can be tilted to adjust the strength of contractions, and included only subjects who are naive to MS. Nevertheless, we think that our blinding methods may be unsuccessful in some patients. Selective refusal by participants in the present study may limit the generalizability of the study results to the wider public. Furthermore, when we first designed the trial, we specified a follow-up period of 6 months for logistical reasons. However, we intend to prolong our follow-up period to a minimum of 1 year, as recommended by guidelines [45]. Amendments have been made and submitted to our local ethics committee. Finally, we selected our sample size based on our primary outcome data analysis method (responder analysis: percentage of subjects who meet primary criterion of response). Our study may be underpowered for determination of statistical significance for the secondary outcome measures.

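### The economic question names conventional therapy as comparator, but the trial compares MS only with sham, so it cannot be answered as written

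*Protocol article*

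**What the plan says.** Under Aims of the study, the protocol article sets out "to prove its overall cost-effectiveness" and asks "Is the use of MS cost-effective compared with the conventional therapy".

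Under Study design it states: "This is a multicenter, randomized, double-blinded, sham-controlled, parallel-group trial in a 1:1 allocation ratio". The Interventions section gives all subjects lifestyle counselling and then says: "In both groups, treatment involves two sessions of 20 minutes each per week for 8 weeks (16 sessions total"). Under Sham magnetic stimulation, "the sham group will undergo the same number, duration and frequency of treatments as the active group using the same MS device". Only coil tilt and intensity differ.

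Under Additional restrictions, "Subjects are prohibited from starting additional specific treatments for SUI, including PFMT"; the list goes on to biofeedback, cones, electrical stimulation and drugs. The Background describes PFMT as the first-line conservative treatment under current guidance.

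The section Health economic evaluation and analysis plans to measure resource use in natural units, with treatment minutes as its example, to price the average use per patient, and to form an ICER. The sensitivity analysis works by "replacing the mean costs and effects with the upper and lower bounds" of their 95 % confidence intervals. The section names no comparator, external data source, model or time horizon.

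**The concern.** An ICER needs a cost and an effect for each of the two options compared. The research question names one comparator and the design supplies another. If the analysis goes ahead as described, an active-versus-sham ratio could be reported as an answer about conventional therapy.

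That ratio is also fragile. A good sham consumes the same staff and chair time as the active treatment. Costed as delivered, it cancels almost the whole cost of MS, and the treatment looks nearly free. The result then depends on how the control was built and says little about the value of the treatment.

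The stated sensitivity analysis would not expose this. It moves costs and effects to their confidence bounds separately, which ignores how cost and effect vary together across patients. When the effect interval lies near zero or crosses it, the resulting ratios are hard or impossible to interpret.

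**Working it through.** **Step 1: does any arm supply the comparator?**
- Arms: active MS and sham MS (Study design; Randomization).
- Conventional treatment: starting it is prohibited in both arms (Additional restrictions).
- Lifestyle counselling: given to everyone (Interventions), so it cancels between arms.
- External data or model: none named in the economic section.

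No cost or effect for conventional therapy comes from this trial.

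**Step 2: treatment resources in the blinded 8 weeks.**
- Sessions per subject: 2 per week x 8 weeks = 16, as the article states.
- Minutes per subject: 16 x 20 = 320 in the active arm and 320 in the sham arm.
- Increment: 320 - 320 = 0 minutes and 0 sessions.
- Energy is the one built-in difference. The sham section gives 136 kJ for the whole sham course and 408 kJ for one active session at full intensity. The active course is at most 16 x 408 = 6,528 kJ. The gap is at most (6,528 - 136) / 3,600 = 1.8 kWh per subject, if energy output is taken as a stand-in for electricity used.

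**Step 3: the ratio under two costings of sham.** Assume that the effect measure is the responder difference in Sample size calculation, 0.60 - 0.30 = 0.30. The economic section does not fix the measure. Let C be the cost of one MS course, which the article does not give.
- Sham costed as delivered: about 0 / 0.30 = 0 per extra responder, whatever C is.
- Sham costed at zero: C / 0.30 = 3.3 x C. For an assumed C of 500 to 2,000 currency units, this is 1,667 to 6,667.

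**Step 4: beyond week 8.** Dissatisfied subjects in either arm may enter an open-label phase, and Table 1 records retreatment or new intervention to week 32. Assume that every non-responder takes a further 16-session course.
- Active: 0.40 x 320 = 128 extra minutes.
- Sham: 0.70 x 320 = 224 extra minutes.
- Increment: 128 - 224 = -96 minutes. With 50 % uptake it is -48 minutes.

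The increment is no longer zero, but the contrast is still not with conventional therapy.

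**Step 5: what the bound swap does to the effect side.** Take 60 per arm, from the enrolment goal of 120, and zero-cost sham.
- Planned rates, 0.60 versus 0.30: SE = sqrt(0.24/60 + 0.21/60) = 0.0866. The 95 % CI is 0.30 ± 1.96 x 0.0866 = 0.130 to 0.470. The ratio runs from C / 0.470 = 2.1 x C to C / 0.130 = 7.7 x C, a 3.6-fold range.
- Illustrative smaller effect, 0.45 versus 0.30 (an assumption, not in the article): SE = sqrt(0.2475/60 + 0.21/60) = 0.0873. The 95 % CI is -0.021 to 0.321. At the lower bound the ratio is negative.

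If sham is costed as delivered, the numerator is about zero and this range means little.

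**The case against.** The strongest reply is that the economic evaluation is ancillary, that the section describes it as still being planned, and that a journal article commonly leaves comparator data, horizon and uncertainty methods to a fuller plan. That is fair for what is merely unsaid. It does not remove the mismatch between the stated question and the stated design.

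A reader might infer that the trial's ICER has zero incremental cost whatever is done. The article does not support that. The zero is exact only for treatment delivered in the blinded 8 weeks with sham priced as delivered. The economic section fixes neither the horizon nor the pricing of sham, and treatment minutes are only an example.

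A reader might also infer from the Discussion remark "If the efficacy of MS is better than PFMT, which has a success rate of approximately" 30 % that the authors plan a comparison with PFMT on mismatched endpoints. The remark is conditional, is not part of the economic analysis, and does not say which endpoint would be set against it. It should not be counted as a fault.

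On the bound swap, the article calls it a sensitivity analysis and never claims a 95 % region for the ratio. A simple deterministic analysis is not an error in itself. What stands is that swapping the bounds separately ignores the correlation and can give ratios with no meaning. This is a method the article states, so it can fairly be improved.

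Finally, costing sham at zero does not turn the sham arm into an untreated group. Sham subjects attend 16 sessions and a 30 % response is anticipated. Zero cost combined with the sham-arm effect joins the cost of one comparator to the effect of another, so it is defensible only as a declared assumption.

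**Conclusion.** The point holds. The question about conventional therapy cannot be answered from this trial as written, and that conclusion rests on no numerical assumption. The available active-versus-sham ratio runs from about 0 to about 3.3 times the course cost, depending only on whether sham is costed as delivered or at zero. That range assumes an 8-week horizon and a responder difference of 0.30 as the effect. Over a longer horizon the increment could be negative, to an extent that depends on open-label uptake.

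The change should be made because a stated aim depends on it. It leaves the primary outcome, the power and the efficacy inference untouched. A full protocol might name an external comparator, but the published text does not, and the aims and the economic section need reconciling either way.

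**What to change.** 1. Reword the third research question and the aim about overall cost-effectiveness as MS versus sham over the randomized 8 weeks.
2. Put the active arm at the full cost of an MS course. State zero-cost sham as an explicit assumption, and note that the sham-arm effect may understate the benefit against no treatment.
3. If a comparison with conventional therapy is still wanted, label it as an indirect model, with a named data source and the same endpoint definition on both sides.
4. Name the effect measure used in the economic analysis.
5. Replace the separate swap of cost and effect bounds with a non-parametric bootstrap of patient-level cost-effect pairs. Report net benefit, that is, the value placed on a unit of effect times the incremental effect, minus the incremental cost. This stays defined when the effect interval crosses zero.

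The cost is a rewording of one question and one aim, plus a modest amount of analysis. No new arm or subjects are needed, and recruitment is already complete. The bootstrap assumes that resource use is kept per subject and not only as averages. The downside is a narrower economic claim.

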**Fig. 1 Fig1:**
[figure not shown]
Trial flowchart

**Table 1 Tab1:** Study design schedule

	Screening and baseline	Treatments					Follow–up		
Visit	0	1	2–7	8	9–15	16	17	18	19
Timeline (wk)	0	1	1–4	4	5–8	8	12	20	32
Screening for eligibility	x								
Informed consent	x								
Demographic data and medical history	x								
Physical examination	x								
Urine analysis	x								
Random blood sugar	x								
UPT	x					x			
Uroflowmetry with postvoid residual (ultrasound)	x					x			
Randomization		x							
MS treatment		x	x	x	x	x			
Adverse events		x	x	x	x	x	x	x	x
Retreatment or new intervention							x	x	x
ICIQ-UI-SF	x			x		x	x	x	x
Incontinence episode diary	x			x		x	x	x	x
1-hr pad test	x			x		x	x	x	x
PFMF (perineometer)	x			x		x	x	x	x
PGI-I				x		x	x	x	x
ICIQ-LUTS-QoL	x			x		x	x	x	x
EQ-5D	x			x		x	x	x	x
Blinding assessment						x			

*Abbreviations: ICIQ-LUTS-QoL* International Consultation on Incontinence Questionnaire–Lower Urinary Tract Symptoms Quality of Life, *ICIQ-UI-SF* International Consultation on Incontinence Questionnaire for Urinary Incontinence Short Form, *MS* magnetic stimulation, *PFMF* pelvic floor muscle function, *PGI-I* Patient Global Impression of Improvement, *UPT* urine pregnancy test

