### Randomization

Subjects will be assigned in a 1:1 allocation to either the active or sham MS group using computer-generated, permuted block randomization, with variable block sizes of four, six and eight, by an independent pharmacist with no clinical involvement in the trial. Details of the allocated group are given in sequentially numbered, opaque, sealed envelopes to an appointed nurse involved in administering the treatments to subjects. The independent pharmacist who generates the randomization list will ensure that the envelopes are opaque and impermeable when held to the light. Additionally, the sealed envelopes are stored in a locked cabinet accessible only by the appointed nurse. Enrollment of subjects (assessment of eligibility, discussion of the trial, obtaining informed consent) will be done by investigators and clinicians who are blinded to treatment allocation. Following enrollment of a subject, the investigator will assign the subject a unique identification number. In the first treatment session for each subject, the appointed study nurses will sequentially open the envelopes. The subject’s unique identification number and date will be written on the appropriate allocated envelope.

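### The design cannot show whether active treatment beyond 16 sessions improves response, because only dissatisfied women who choose to continue get more and nobody is assigned to stop

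*Protocol article*

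**What the plan says.** In the protocol article, Aims of the study lists two questions for the period after the first 2 months of treatment. The second is "Does longer treatment with active MS improve treatment response in the initial active group". The Background also names "How many sessions are needed" among the open issues that it says call for a high-quality randomised trial.

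Under Interventions, both arms receive two sessions a week for 8 weeks, 16 in all. After that, "subjects who are not satisfied with their treatment outcome will be given the opportunity to enroll in an open-label phase, regardless of their treatment allocation".

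The Randomization section describes one allocation, opened at the first treatment session: "Subjects will be assigned in a 1:1 allocation to either the active or sham MS group". The text mentions no second allocation at week 8.

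Table 1 schedules the ICIQ-UI-SF at baseline, week 4 (visit 8), week 8 (visit 16) and weeks 12, 20 and 32. At the last three it also has a line for "Retreatment or new intervention". The Statistical analysis section fits time, allocation and their interaction. It gives no separate term or contrast for treatment length.

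**The concern.** The question is causal: does more treatment improve response? An answer needs comparable active-arm women, some of whom continue and some of whom stop at 16 sessions. The design does not supply them. Entry to further treatment depends on a poor perceived outcome at week 8 and on the woman's own choice, and that treatment is open-label.

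Two comparisons are left, and each is biased:

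- **Continuers against active-arm women who stop.** The stoppers are satisfied or declined the offer. This largely sets poorer responders against better ones and tends to make extra sessions look useless or harmful.
- **Continuers against their own week-8 score.** Women selected for a poor value tend to score better when measured again. Time and open-label expectation may add to this, so extra sessions tend to look helpful.

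The sham arm does not fill the gap, because dissatisfied sham women may enter the same open-label phase over the same period.

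At stake is a stated research question whose answer could change sign with the comparison chosen, and which could feed advice on how long to treat. The Background criticises earlier studies for lacking a placebo group. For this question the extension has the same weakness.

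**Working it through.** **1. The plan's own figure.** The article gives no figure for the longer-treatment question. Its sample size concerns active versus sham at week 8, with inputs 0.60 and 0.30, α = 0.05 (taken as two-sided) and power 80 %.

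- n per arm = 2·p̄(1 − p̄)(z₀.₉₇₅ + z₀.₈₀)²/δ² = 2 × 0.45 × 0.55 × (1.960 + 0.842)²/0.30² = 43.17. This rounds up to 44 per arm, 88 in total, as stated.
- With 25 % dropout, 88/0.75 = 117.3, so 118. The stated goal is 120.

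The calculation reproduces, but it gives no precision for anything after week 8.

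**2. Who is compared with whom after week 8.**

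| Group | How formed | Treatment after week 8 |
|---|---|---|
| Active arm, continue | dissatisfied and chose to enter | further open-label sessions |
| Active arm, stop | satisfied, or declined | none in the open-label phase; followed to week 32 |
| Sham arm | dissatisfied women may also enter | mixed |

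No row is formed by a random assignment of treatment length.

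**3. Size of regression to the mean with no true effect of extra sessions.**

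From the protocol: response is a fall of at least 5 points in ICIQ-UI-SF, and active response is 60 %, so 40 % are non-responders at week 8.

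Assumed, not in the documents: normally distributed change scores with the same mean and SD at week 8 and at the next assessment; SD 4 to 5 points; correlation r between the two change scores of 0.6 to 0.9; non-response standing in for dissatisfaction.

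Let z be the 40 % point of the standard normal, z = −0.253, with density φ(z) = 0.386.

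- Share of week-8 non-responders who meet the criterion next time = P(Z₁ < z, Z₂ ≥ z)/0.40, with correlation r. The SD cancels.
- Mean apparent gain = (1 − r) × SD × φ(z)/0.40 = 0.966 × (1 − r) × SD.

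| r | Later response among week-8 non-responders | Mean gain, SD 4 | Mean gain, SD 5 |
|---|---|---|---|
| 0.6 | 36 % | 1.5 | 1.9 |
| 0.7 | 31 % | 1.2 | 1.4 |
| 0.8 | 25 % | 0.8 | 1.0 |
| 0.9 | 17 % | 0.4 | 0.5 |

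A simulation under the same assumptions agrees with these values.

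**4. In women.** With 60 per arm, 0.40 × 60 = 24 active-arm non-responders would be expected at week 8. If all were reassessed, between 0.17 × 24 ≈ 4 and 0.36 × 24 ≈ 9 would count as new responders although the extra sessions did nothing.

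**The case against.** The strongest reply is that the article does not say how the extension will be analysed. The question is neither a primary nor a secondary outcome, carries no power claim, and rests on a phase that the article itself calls open-label. Analysis detail may sit in the full protocol or the SAP. This stands as far as it goes: neither biased comparison is written into the article, and the size shown above rests on assumed SDs and correlations. It does not remove the point. The gap comes from how women enter the extension, and no later analysis text can supply a control that was never assigned. The flowchart is not shown, but nothing in the text suggests a second randomisation.

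Three stronger readings are tempting, and the documents do not support them:

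- **Nobody stops at 16 sessions, so nothing can be learned.** Women who do not enter the open-label phase stop at 16 and are followed at weeks 12, 20 and 32. They are not a comparable control, but they exist, and the course of the continuers can still be described.
- **Weeks 4 and 8 already give a randomised comparison of treatment lengths.** Nobody is randomised to 8 or 16 sessions; only active versus sham is randomised. Both visits lie within the first 16 sessions, whereas the question concerns the time after them. Stimulation intensity also changes over sessions in both arms, so a growing difference would mix session number, elapsed time and intensity.
- **The plan leaves the week-4 and week-8 data unused.** The planned allocation-by-time model already contains that contrast. It is only not labelled as bearing on treatment length.

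**Conclusion.** The point holds in a limited form. The design cannot support a causal answer about active treatment beyond 16 sessions; it can support a descriptive one. Regression to the mean alone could turn 17 % to 36 % of week-8 non-responders into apparent responders, with a mean apparent gain of 0.4 to 1.9 points, up to about two fifths of the 5-point criterion (1.9/5 = 0.38). This range rests on the protocol's 60 % active response and on the assumed correlations, SDs and normality. It illustrates the size and does not predict it, because actual entry depends on dissatisfaction and choice, not on the 5-point rule.

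A reader might infer that the trial's main result is compromised. It is not: the primary active-versus-sham comparison is at week 8, before the open-label phase opens. The defect lies in one stated research question and in what may be concluded from it.

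**What to change.** - Reword the question in Aims of the study as descriptive: what is the response among active-arm women who choose further open-label sessions after week 8?
- Report it only as within-woman change from week 8, labelled uncontrolled. State beside the result that regression to the mean, time and open-label expectation cannot be separated from any effect of the sessions.
- Make no causal claim about more than 16 sessions, and do not compare continuers with stoppers.
- The active-minus-sham difference at weeks 4 and 8, available from the planned model, may be reported as how benefit accrues up to 16 sessions. It should not be presented as a randomised comparison of durations.

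The cost is a few sentences; no new data are needed. Trial status says that recruitment is complete and follow-up continues, so the change in reporting can still be fixed in advance. The downside is that the trial no longer claims to show an effect of treatment beyond 16 sessions. Randomising non-responders a second time is not proposed. About 24/2 = 12 per group would give power of only about 0.31 to 0.39 for a 30-point difference, assuming 10 % to 30 % later response without further sessions.
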